## Abstract

**Background:**

Electromagnetic navigation bronchoscopy (ENB) is an emerging advanced imaging-guided bronchoscopy technique for diagnosing peripheral lung lesions. However, the selection strategy for the optimal biopsy device and whether adopting a multi-tool strategy increases the diagnostic yield remains undetermined. The CONFIDENT-ENB trial (NCT05110131) is a prospective randomized study on ENB, performed in a least-invasive setting. The primary aim is to evaluate whether a combination of needle aspiration and forceps biopsy improves the diagnostic performance, and assess the comparative diagnostic value and discordance of the two devices.

**Methods:**

The trial will recruit 142 participants with lung lesions suspected of malignancy who are eligible for an elective ENB procedure under moderate sedation. Participants will undergo ENB-guided needle aspiration and forceps biopsy in a randomized order without the use of any complementary techniques. All participants will be followed up subsequently for up to 12 months to conclude the final diagnosis of the biopsied lesions. Primary outcomes include the diagnostic yield and sensitivity of each biopsy modality and the diagnostic yield of the combined modalities.

**Discussion:**

The CONFIDENT-ENB trial will prospectively evaluate the synergistic effectiveness and comparative accuracy of ENB-guided needle aspiration and forceps biopsy in a least-invasive setting. The results are expected to improve our understanding of the optimal tool-selection strategy for ENB.

*Trial registration*: ClinicalTrials.gov (NCT05110131). Prospectively registered on 5 November 2021.

## Background

Lung cancer remains the common most cause of cancer-related deaths among both men and women globally [1]. Early and accurate diagnosis is important to facilitate curative intent. Recently, widespread efforts for early detection and implementation of lung cancer screening with low-dose chest computed tomography (CT) have resulted in a considerable increase in the identification of peripheral lung lesions, suspected of being lung cancer, which require diagnostic evaluation [2–4]. The histopathological diagnosis of pulmonary lesions is a challenging process that has been attempted using various techniques. According to current clinical practice guidelines, the least invasive approach with the highest yield is recommended [5–7]. For peripheral lesions that are difficult to reach with conventional bronchoscopy, transthoracic needle aspiration (TTNA) is commonly used. However, despite a good sensitivity of approximately 90%, TTNA carries a reported pneumothorax rate of > 18% of the biopsied cases [8, 9].

Recently, in an attempt to improve the yield and safety of flexible bronchoscopy, several image-guided technologies have been developed [10]. Emerging bronchoscopy techniques include electromagnetic navigation bronchoscopy (ENB), which involves generating an electromagnetic field around the patient. This technique allows physicians to access peripheral lung lesions through a minimally invasive technique using an image-guided flexible catheter and a dedicated navigation software system. Although the reported diagnostic performance of ENB varies between studies, it is fairly accepted to yield good accuracy in diagnosing malignancy with a yield of over 70% and a markedly lower complication rate (< 3% for pneumothorax) than TTNA [11–13]. According to current guidelines, ENB is recommended for peripheral lung lesions beyond the reach of conventional flexible bronchoscopy alone [4, 5].

For diagnostic bronchoscopic procedures, including ENB, the most commonly used sampling methods are forceps biopsy and needle aspiration [14, 15]. Previous studies suggest that the diagnostic yield may be related to the choice of biopsy tool [16–18]. Particularly, several studies have reported a better diagnostic yield with the aspirating needle than with other transbronchial techniques [16, 17, 19, 20]. Furthermore, a few studies suggest that the use of a multi-tool strategy can improve the diagnostic yield [19, 21, 22]. However, multiple studies that have published real-world data on ENB have reported the use of a single-tool strategy with low use of the aspirating needle, which may have contributed to the overall low diagnostic yield of ENB [16, 23–25]. A disparity exists in the context of a higher reported diagnostic yield with the aspiration needle and the actual use in clinical practice. Therefore, the synergistic benefits of needle aspiration and forceps biopsy possibly derived from the relative accuracy and discordance of needle aspiration and forceps biopsy with ENB warrant further examination in a prospective, controlled study. The CONFIDENT-ENB (“COmparison and synergistic evaluation of Needle aspiration and Forceps bIopsy for Diagnosing pulmonary lEsioNs wiTh Electromagnetic Navigation Bronchoscopy”) trial is a prospective trial that aims to evaluate whether combining ENB-guided needle aspiration and forceps biopsy provides synergistic benefits, with comparison of the diagnostic performance of the two methods.

## Methods/design

### Study design and subject eligibility

We designed a prospective, randomized trial to evaluate the synergistic diagnostic yield of ENB-guided needle aspiration biopsy and ENB-guided forceps biopsy by performing biopsy with both the devices in a random order (Fig. 1). This study aims to enroll approximately 142 participants from a tertiary center in South Korea by 11 pulmonary physicians. All consecutive patients over the age of 18 years who are candidates for an elective ENB procedure for histopathological evaluation of peripheral lung lesions suspected of malignancy but predicted to be unreachable with conventional bronchoscopy alone are eligible for enrollment. The exclusion criteria are: (1) patients unable or unwilling to provide informed consent or comply with the follow-up schedule; (2) patients who have participated in an investigational drug or device research study within 90 days of enrollment, with possible interference with this study; (3) patients with a history of intolerance to moderate sedation or allergies to any of the sedatives planned to use, those with comorbidities contraindicating the bronchoscopy procedure, those on mechanical ventilation or who underwent a tracheostomy, or those who are pregnant; (4) patients with multiple lesions that need to be sampled with ENB-guidance; and (5) patients who were initially planned to undergo ENB but successfully underwent biopsy from a visible endobronchial tumor lesion, which precluded the need for electromagnetic navigation, or those who failed to perform ENB-guided biopsy with both modalities.

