### Randomization and baseline evaluation

After providing informed consent, the participants will be randomly allocated to a study group (needle precedence group or forceps precedence group). They will initially undergo ENB-guided biopsy with the modality of the allocated group (needle or forceps) followed by a biopsy with the other modality. Randomization will be performed by an independent statistician using a computer-generated list using SAS version 9.4 (SAS Institute, Cary, NC, USA). The attending physicians have no role in the assignment process and will be blinded to the allocation. The physicians who will perform the ENB procedure are also blinded to the allocation until the preparation of ENB on the day of the procedure.

The enrolled participants will be evaluated for demographic, clinical, and radiological characteristics at baseline (within 30 days of the procedure) and on the procedure day. The complete list of baseline demographic data and lesion characteristics evaluated with the pre-procedural chest CT is listed in Table 1. Additionally, the pre-procedural probability of malignancy of the lesion will be evaluated for each lesion using the Brock model [3].

**Table 1 Tab1:** Basic characteristics of the participants

Demographics
Age (years)
Sex
Race
Smoking status
Pack-years smoked
Family history of lung cancer
Clinical characteristics
Performance status
History of lung cancer diagnosis
History of malignancies other than lung cancer
Prior invasive lung procedures and surgery
Radiological characteristics
Lesion location (lung lobe)
Lesion type (solidity)
Lesion size
Size of solid proportion
Lesion shape (speculated margin, cavity formation, bubble lucency)
Pre-procedural probability of malignancy
Distance from lesion to pleura
Emphysema surrounding lesion
Interstitial fibrosis surrounding lesion
Bronchiectasis surrounding lesion
Presence and type of bronchus sign
Combined lymphadenopathy
Positivity on positron emission tomography (if applicable)
Procedural characteristics
Preceded modality
Capability to navigate and localize the lesion
Number of biopsy attempts (for each modality)
Acquisition of a core tissue available for histologic examination (for each modality)
Procedure duration
Sequential linear EBUS for nodal staging
Total dose of sedatives used

*EBUS* Endobronchial ultrasound

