**Secondary endpoints**
- Secondary outcomes will be calculated separately for needle aspiration and forceps biopsy
- Navigation success:
Target lesion successfully reached with the biopsy tool; identified by the dedicated navigation software
- Procedure time:
Duration from the initial introduction of the tool to the final removal of the biopsy tool
- Time per biopsy attempt:
Procedure time divided by the number of biopsy attempts
- Successful acquisition of core tissue:
Acquisition of a fresh tissue available for histological examination
Procedure-related adverse events
-Pneumothorax
Grade 1: asymptomatic; clinical or diagnostic observations only; intervention not indicated
Grade 2: symptomatic; intervention indicated (e.g., thoracic tube insertion without pleurodesis)
Grade 3: pleurodesis and/or operative intervention indicated; hospitalization indicated
Grade 4: life-threatening consequences; urgent intervention indicated
Grade 5: death
Bronchopulmonary hemorrhage
Grade 1: mild symptoms: intervention not indicated
Grade 2: moderate symptoms: invasive intervention not indicated
Grade 3: transfusion indicated; invasive intervention indicated; hospitalization
Grade 4: life-threatening consequences; intubation or urgent intervention indicated
Grade 5: death
Respiratory failure:
Life-threatening situations with urgent intubation or ventilator support indicated

*ENB-guided biopsy* Electromagnetic navigation bronchoscopy-guided biopsy

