### Primary statistical plan and sample size considerations

The sample size was calculated in order to determine a 15% difference in the diagnostic yield between the individual modalities and their combined use owing to the expected better and synergistic diagnostic yield. The estimated difference in the diagnostic yield (67% vs. 82%) is based on previously conducted large-scaled observational studies and meta-analyses that suggested an improved diagnostic yield with the use of needle aspiration and a combination of both modalities [11, 12, 14, 16]. The calculation was based on this difference in the diagnostic accuracy for equality of paired proportions with a two-sided significance level of 0.05 and 80% power. Assuming that the response with needle biopsy is independent of the response with forceps biopsy, the percentage of participants with discordant results for the two modalities was estimated to be 39%. With an estimated dropout rate of 5% due to the loss of patients during follow-up, we estimated a sample size of 142 participants (71 in each group, and 142 biopsies for each modality and combination). The sample size was calculated using PASS 2021 (NCSS, LLC., Kaysville, UT, USA).

Baseline demographic, clinical, and radiological characteristics of the participants as well as the procedural details and outcomes will be presented as means with standard deviation (SD) for continuous data and frequencies with proportions for categorical data. Characteristics will be analyzed using the *t*-test (or Wilcoxon’s rank-sum test) for continuous variables and the chi-square test (or Fisher’s exact test) for categorical variables. Since each patient will have two results from separate modalities, it should be considered that two outcomes from the same patient are likely to be more similar than two results from different patients. To compare the paired proportions, McNemar’s test will be used. A *p*-value < 0.05 indicates statistical significance. All analyses will be performed using STATA version 16.0 (StataCorp., College Station, TX, USA). A preliminary analysis is prespecified when all the enrolled participants undergo ENB with available initial pathological reports and 1-month follow-up.

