When performing ENB, the decision to choose the relevant biopsy tool(s) is important. Several studies have suggested that transbronchial needle aspiration (TBNA) can increase the diagnostic yield of conventional bronchoscopy and guided bronchoscopy [16, 18, 20, 34]. However, TBNA also includes limitations in approaching lesions in the upper lobes or superior segment of the lower lobes because the needle may not be able to pass through sharp angles. Despite the possible benefits, even in expert centers, TBNA is underused in real-world practice [15, 16, 23]. Similarly, for ENB, transbronchial forceps biopsy remains the mainstream modality for tissue sampling followed by needle aspiration [14, 24, 25]. Several studies have suggested a higher diagnostic yield with ENB-guided TBNA than forceps biopsy, while few studies have suggested that using multiple tools may be more effective than single-tool strategies [11, 12, 19]. When performing ENB, multiple factors such as its usage patterns, market availability, and reimbursement factors influence the choice of the biopsy tool other than the expected efficacy of any individual tool or combinations of multiple tools. Especially, the cost of using an additional tool is an important limiting factor in choosing a multi-tool strategy without clear benefits. Therefore, relevant comparisons are required between the diagnostic performances of forceps and aspirating needle biopsy, which are the two modalities that are expected to provide the highest efficacy and are most commonly used in clinical practice. Furthermore, data regarding whether a combination of the two modalities would have synergistic effects on the overall diagnostic yield would be particularly important. These needs were the essential driving forces behind the planning and design of the current trial. To minimize possible biases and inconclusiveness resulting from the use of other complementary imaging or biopsy tools and different sedation methods, we designed this study such that the procedure can be performed in a least-invasive setting under moderate sedation without the use of additional techniques other than ENB. Our study settings reflect the target circumstances of minimal invasiveness in diagnosing lung lesions using guided bronchoscopy. Furthermore, our design reflects the setting accessible to the maximum number of physicians who perform ENB in clinical settings with limited access to general anesthesia or other techniques, such as ROSE. The navigation system used for ENB will also be controlled and unified into the Spin Thoracic Navigation System.

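### Exclusion criterion 5 removes randomised patients for procedural failure: absolute yield is biased upward, and the tool comparison is distorted only under one of its two readings

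*Protocol article*

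**What the plan says.** The eligibility section of the protocol article (Study design and subject eligibility) lists five exclusions. The fifth has two limbs. The first covers "patients who were initially planned to undergo ENB but successfully underwent biopsy from a visible endobronchial tumor lesion". The second covers "or those who failed to perform ENB-guided biopsy with both modalities".

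Under Randomization and baseline evaluation, allocation follows consent: "After providing informed consent, the participants will be randomly allocated to a study group (needle precedence group or forceps precedence group". The physicians performing the procedure are "blinded to the allocation until the preparation of ENB on the day of the procedure".

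Table 2 calculates the primary measures separately for needle, forceps and the combination. It puts definite diagnoses over lesions biopsied, not over patients randomised or patients who started the procedure. Navigation success is a secondary endpoint, also calculated per tool: "Target lesion successfully reached with the biopsy tool; identified by the dedicated navigation software". The Procedures section records localisation and approach as well as the number of biopsy attempts.

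The Discussion notes that the needle may have trouble in the upper lobes and the superior segment of the lower lobes, "because the needle may not be able to pass through sharp angles". The sample size makes one allowance: "With an estimated dropout rate of 5% due to the loss of patients during follow-up".

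**The concern.** The second limb is a procedural result placed among the eligibility criteria. It cannot be known at consent or at randomisation. It arises in the hands of an operator who by then knows the order.

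It is also ambiguous. It may exclude a patient when either tool could not be used, or only when neither could. The sample-size section counts 142 biopsies for each modality, which fits the either-tool reading better, but the text does not settle it.

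A tool that cannot sample the lesion has failed in the sense that matters for yield. Under both readings, patients with no biopsy leave the denominator. Under the either-tool reading, lesions that one tool cannot sample leave as well, and the Discussion gives a reason why this would affect the needle in particular. The absolute yields, and possibly the gain from combining the tools, would then describe lesions selected for procedural success. The stated target is consecutive candidates for the procedure.

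**Working it through.** **Inputs from the protocol.** Single-tool yield 67%, combined yield 82%, difference 15 points, discordance 39%, two-sided 0.05, power 80%, dropout 5%, total 142 (Primary statistical plan and sample size considerations). **Not in the documents:** any rate of procedural failure. The shares f and g below are assumptions, shown at 5% and 10%.

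**1. The plan's own figure.** The paired-proportions formula with the stated discordance gives

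n = [1.96·√0.39 + 0.8416·√(0.39 − 0.15²)]² / 0.15² = 133.7, rounded up to 134; 134/0.95 = 141.05, rounded up to 142.

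The stated 142 reproduces, so the point is not an arithmetic error.

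**2. Both readings: no biopsy by either tool (share f).** Treat 67% and 82% as the reported yields after exclusion. Yield among all who start navigation is the reported yield × (1 − f).

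| f | single tool | combined | inflation 1/(1 − f) |
|---|---|---|---|
| 5% | 0.67 × 0.95 = 63.7% | 0.82 × 0.95 = 77.9% | 1.05 |
| 10% | 0.67 × 0.90 = 60.3% | 0.82 × 0.90 = 73.8% | 1.11 |

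The 15-point difference shrinks in the same ratio, to 14.25 and 13.5 points. The removed patients are non-diagnostic with both tools, hence concordant. McNemar's test uses only discordant pairs, so its result does not change.

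**3. Either-tool reading only: lesions that forceps can sample and the needle cannot (share g).** Now treat 67% and 82% as the yields before exclusion, and assume 67% forceps yield in the dropped lesions.

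- Needle after exclusion: 0.67/(1 − g). At 5%, 70.5%; at 10%, 74.4%.
- Combined after exclusion: (0.82 − 0.67g)/(1 − g). At 5%, 82.8%; at 10%, 83.7%.
- Gain over needle: 12.3 points at 5% and 9.2 points at 10%, against 15.
- Forceps stays at 67% by assumption, because (0.67 − 0.67g)/(1 − g) = 0.67. The gain over forceps therefore rises slightly, to 15.8 and 16.7 points. The understatement concerns the tool that failed.

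The direction is the same if 67% and 82% are taken as the reported values. For all patients, needle yield is then 0.67(1 − g) and combined yield is 0.82(1 − g) + 0.67g. The gain over needle is 17.6 points at 5% and 20.2 points at 10%, where 15 would be reported.

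**4. Navigation success.** Under the both-tools reading, take 5% double failures and a further 5% needle-only failures, and suppose that every failure to biopsy was a failure to reach the lesion. Needle navigation success among retained patients is 0.90/0.95 = 94.7%, against 90% of all. With 10% needle-only failures it is 0.85/0.95 = 89.5%, against 85%. The figure is too high, but it is well short of 100% and can still differ between tools.

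**The case against.** Four replies have weight.

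- Only the order of the tools is randomised and every patient is meant to receive both. The main comparisons are within patient, so the exclusion does not unbalance two treatment arms as it would in a parallel-group trial. This stands. It does not protect the absolute yields, nor the comparison when selection acts on one member of the pair.
- Performance in lesions sampled by both tools is a legitimate, narrower question and suits the aim of relative accuracy and discordance. This also stands, and is a reason to keep that set as a secondary analysis.
- The criterion concerns whether biopsy was carried out, not whether it was diagnostic. Non-diagnostic samples stay in. This is correct and limits the bias to procedural failures.
- The documents give no failure rate, so the sizes are hypothetical. This is true of the sizes but not of the direction for absolute yield.

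The planned STARD and CONSORT reporting would show the exclusions but would not alter the denominator.

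A reader might infer that navigation success is close to 100% by definition. The documents do not support that. The endpoint is read from the navigation software, and localisation is recorded apart from biopsy, so a lesion biopsied but not reached can remain. Under the both-tools reading single-tool failures remain too. A reader might also infer that patients lost to follow-up are dropped and inflate yield further. No section removes them: the 5% is a sample-size allowance, and a biopsied patient who is later lost is still a biopsied lesion in Table 2.

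**Conclusion.** The point holds in limited form. The second limb of criterion 5 is a post-randomisation exclusion based on procedural success, and its wording is ambiguous. Together with the Table 2 denominator it biases absolute yield upward under either reading. The inflation is 1/(1 − f), or about 5% to 11% in relative terms if 5% to 10% of patients have no biopsy by either tool.

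Distortion of the tool comparison depends on the either-tool reading. In that case, with 5% to 10% forceps-only lesions and 67% forceps yield in them, needle yield is overstated and the gain over needle is understated by roughly 3 to 6 points. That bias runs against the trial's synergy hypothesis. Under the both-tools reading the McNemar comparison is unaffected. Navigation success is selected on a closely related event and so is biased upward to the extent that unsampled lesions were also unreached.

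**What to change.** - State which reading of criterion 5 is meant, and remove the tool-failure clause as an exclusion.
- For yield and navigation success, use as denominator all randomised patients in whom navigation was started, and amend Table 2 to match. Count a tool that obtained no sample as non-diagnostic for that tool. Take navigation success from the software record.
- Keep the set biopsied with both tools as a secondary analysis.
- Report all exclusions by allocated order, including visible endobronchial tumours.
- Follow the retained patients to the 12-month diagnosis, so that the measures that depend on it can be given in the same set.

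The cost is an amendment to the wording, somewhat lower reported yields, and 12-month follow-up of a few more patients. The procedural data are already recorded under Procedures. Nothing in the article says whether patients excluded so far are being followed. Since enrolment was in progress at the time of writing, that should be checked early.
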